### Hypotheses

We will test the following detailed study hypotheses with respect to the main outcome: reduction in the number of days of cannabis use over the past week, comparing the baseline, 6-week, and 3-month follow-up assessments:

An adherence-focused, guidance-enhanced, Web-based self-help program with a social presence (study arm 1) is more effective than an adherence-focused, guidance-enhanced, Web-based self-help program with no social presence (study arm 2) at reducing cannabis use.An adherence-focused, guidance-enhanced, Web-based self-help program to reduce cannabis use with a social presence (study arm 1) is more effective than TAU (study arm 3) at reducing cannabis use.An adherence-focused, guidance-enhanced, Web-based self-help program to reduce cannabis use without a social presence (study arm 2) is more effective than TAU (study arm 3) at reducing cannabis use.Participants in study arm 1 will demonstrate better adherence than participants in study arm 2 over the 6-week intervention.

We have similar expectations with respect to our secondary cannabis-related outcomes and will explore frequently co-occurring mental disorders as predictors of adherence and outcomes. Specifically, we also want to explore, for the first time, the influence of attention deficit hyperactivity disorder (ADHD) symptoms on adherence to and outcomes from a Web-based intervention among problematic cannabis users.

### Intervention

CANreduce is an automated Web-based self-help tool developed by the Swiss Research Institute for Public Health and Addiction (ISGF) and and the Arud Centre for Addiction Medicine to reduce cannabis consumption in problematic cannabis users. The Web-based self-help intervention consists of a dashboard, a consumption diary, and eight modules designed to reduce cannabis use based on the principles of MI, self-control practices, and CBT methods. Participants can study all of the modules at their own pace and in whatever order they choose, though a specific order is advised.

As CANreduce 2.0 is regarded as a medical device because of the European Union guidelines 93/42/EWG and 2007/47/EWG, its conformity has been assessed, and potential risks have been evaluated. It is now fully certified in European conformity.

### Active Study Arms

The following elements of CANreduce will be used in both active treatment arms in this study (study arms 1 and 2). The social presence enhancements added just to the program offered to study arm 1 subjects will be described in the *social presence* section below.

#### Start Page

Before actual registration or log-in, a video is accessible in which the scientific director of the ISGF gives a quick introduction to CANreduce. This introduction can also be read as text and aims to motivate eligible individuals to participate in the study.

#### Dashboard

The dashboard (see Figure 2) serves as the central hub, displaying useful information at a quick glance. On the dashboard, participants can see the date when they started the program and how many days remain for them in it. It also displays the dates of the two follow-up assessments and indicates when they have been completed. The same is true of the individual intervention modules, and by clicking a link, participants will be taken to the page in the module where they left off the last time they logged in. There is also a way for subjects to directly enter cannabis consumption data over the preceding week, which then displays a consumption graph.

**Figure 2 figure2:**
[figure not shown]
Dashboard for study arm 1 (translated from German to English for publication purposes only).

**Figure 3 figure3:**
[figure not shown]
Main menu (translated from German to English for publication purposes only).

#### Self-Help Intervention Modules

There are eight self-help intervention modules that are the same for both active treatment groups in terms of the information presented. They are depicted on intervention website’s main menu page (see Figure 3), as well as on the dashboard. Participants are encouraged to complete either one or two of these modules each week and to complete all of the modules in order, though they can access all modules right away. It is also stated that they should feel free to jump directly to modules they feel could be of importance at the moment and to repeat any modules they feel they either especially need to take a second look at, or that they perceive to be especially helpful within the 6 weeks of the program.

A bar in the module overview will indicate the progress they have made with each module; that bar is fully green when the entire module is completed.

The eight modules are summarized in Table 3 and are described below.

##### Module 1: Introduction

In this module, which is largely based on MI techniques, a general overview of the program is given, and fictional companions are introduced. Additionally, participants are encouraged to state their personal reasons for and against their cannabis consumption, which they can review at any time, so they may reflect on what they could gain by successfully completing the program.

##### Module 2: Identifying Risky Situations

Apart from identifying personal situations in which participants could find it difficult to stand by their set consumption goals and working through these scenarios so they are better prepared when they arise, another focus of this module is on seemingly irrelevant decisions and chains of events that can potentially result in unplanned cannabis use. This is an area also explored in traditional CBT.

##### Module 3: Working on Needs

In this module, participants learn skills to help them strengthen their social contacts, decrease possible ruminations, and develop healthier sleeping habits. The importance of sleep and its impact on quality of life is explained. Participants are encouraged to install some rules or rituals to improve their sleeping quality (eg, no big meals or sports in the evening and taking time to unwind the day). Rumination and its impact on well-being is explained, and several techniques are presented to counteract such behavior (eg, thought stop, an audio file with a *passing clouds meditation*, or refocusing on positive things we are grateful for). Finally, social contacts and their link with mood are explained. Participants are encouraged to list people they wish to be in closer contact with, what they could do about it, and what negative beliefs inhibit them from doing so.

##### Module 4: Craving

Here, the concept of craving is explained with its physical and mental aspects for which participants are encouraged to state examples from their own experience. The key concept of triggers (conditioned stimuli) is explained and its link to risk situations, making module 2 worth a suggested revisit. Five possible ways to deal with craving are presented: distraction, talking about craving, mindful experiencing of craving, envisioning negative consequences of consumption, and self-talk.

##### Module 5: Dealing With Relapses

Temporary relapses can happen, but they should not decrease a person’s motivation to achieve their personal consumption goal or be cause for grievance. In this module, participants are taught skills for relapse prevention and to not see relapses as catastrophic events, but rather to learn from them and view their consumption goals as a long-term process.

##### Module 6: Working on Problems

The relationships between cannabis consumption, problems in life, and mild depressive symptoms are highlighted in module 6. Here, participants learn how to deal with problems that they cannot personally affect and are shown problem-solving skills to help them to deal with problems that are seemingly too large to tackle.

##### Module 7: Saying “No”; Refusal Skills

In this module, different ways to strengthen refusal skills are taught to decrease the person’s risk of a relapse whenever and wherever they find themselves in high-risk situations.

##### Module 8: Preserving Achievements

In the eighth and final module, participants are encouraged to review their work in the program and then generate a list of five personalized points that can help them to secure their achievements once their participation in the program is completed.

#### Fictional Companions

Six fictional companions appear within the modules at key points, with the goal of encouraging reflection on certain questions raised by the modules. This is done by the companions thinking out loud, sharing their thoughts on issues raised in written form. Participants can choose one character that best fits their own situation but can also click through the input provided by the other five companions.

#### Consumption Diary

Participants are encouraged to fill out their cannabis consumption diary completely on at least a weekly basis. They can enter their goal about how much they want to use in upcoming days and how much they actually did use in past days in terms of the number of individually standardized joints. 

This individual joint is defined at the start of the program where participants can select between (1) indoor, outdoor, or resin; (2) mixed with or without tobacco; and (3) six different amounts of the substance varying from 67 mg to 500 mg depicted with six photos of unrolled joints corresponding to the type selections from (1) and (2).

**Table 3 table3:** Overview of contents and therapeutic approaches in the modules.

Module	Contents	Therapeutic approach
Module 1: Introduction	General overview Introduction of fictional companions Reflection on personal cannabis consumption	Based on motivational interviewing (MI) techniques [30]
Module 2 : Identifying risk situations	Identifying personal high-risk situations Recognizing seemingly irrelevant but triggering decisions	Cognitive behavioral therapy (CBT) approach to relapse prevention [31]
Module 3: Working on needs	Strengthening social contacts Decreasing excessive ruminations Developing healthier sleeping habits	Behavioral activation approach [32]
Module 4: Craving	Concept of craving Ways to deal with feelings of craving	Based on CBT [33]
Module 5: Dealing with relapses	Relapse prevention Dealing with relapses	CBT approach to relapse prevention [31]
Module 6 : Working on problems	Relationships between consumption, problems, and depressive symptoms Skills to deal with solvable and unsolvable problems	Social problem-solving approach [34]
Module 7: Saying "no"; refusal skills	Strengthening refusal skills for use in high-risk situations	Based on CBT [33]
Module 8: Preserving achievements	Review of program List of five personalized points to help secure achievements after the program is complete	Based on MI techniques [30]

Overall, there are 36 different photos made for this selection procedure [10,13]. A graph is generated live with these data inputs and provides the participant with visual feedback. The ability to anonymously set daily consumption goals could possibly counteract the self-deception often seen in face-to-face drug counseling and strengthen the self-efficacy of users. By adding this consumption diary to both active study arms, Mohr’s accountability factor—*goal setting*—is also integrated into the program.

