### Measurements

Table 4 provides an overview of measurements. Sociodemographic data will include subject gender, age, and level of education.

The primary outcome of interest will be the number of days of cannabis use on the preceding 7 days according to the Time-Line-Follow-Back method [35,36].

Secondary outcomes of interest will include the quantity of cannabis used in the previous week, in standardized cannabis joints (as indicated in the consumption diary as well, as per Schaub et al [10]). Participants can choose between three different cannabis forms presented in photographs and in the second step between five different standard joints for each category (1/10 g, 1/6 g, 1/4 g, 1/3 g, and 1/2 g content pictures). These joints are either pure cannabis or cannabis mixed with tobacco. Finally, every participant has his or her personal standard tobacco cigarette, a ruler with centimeter and millimeter scales, the fraction amount in grams, and an open 10 cm paper prepared to roll a joint and containing the cannabis plant- or resin-tobacco mixture or pure cannabis presented in his or her consumption diary. Further secondary outcomes are the presence and severity of a cannabis use disorder (Cannabis Use Disorder Identification Test-Revised, CUDIT-R); the severity of cannabis dependence (Severity of Dependence Scale, SDS); the use of alcohol, tobacco, or other illicit drugs besides cannabis (Fragebogen Substanzanamnese, FDA); changes in depression, anxiety, and attention deficit symptoms (Center for Epidemiologic Studies Depression Scale, CES-D; general anxiety disorder-7, GAD-7; and Adult ADHD Self-Report Scale-V1.1, ASRS-V1.1); the Short Screening Scale for Diagnostic and Statistical Manual of Mental Disorders, 4th edition (DSM-IV) posttraumatic stress disorder (PTSD); client satisfaction (Client Satisfaction Questionnaire adapted to Internet-based interventions, CSQ-I); and treatment adherence. The perceived relationship between the user and the eCoach will be assessed at the end of the program using the Working Alliance Inventory [37] adapted for Web-based interventions (WAI-TECH).

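### The secondary quantity outcome is counted in each participant's own joint, which may hold 67 mg to 500 mg, so counts are not comparable in mass between participants

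*Protocol article*

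**What the plan says.** Measurements, in the Protocol article, gives the secondary outcome as the "quantity of cannabis used in the previous week, in standardized cannabis joints" and refers to the diary and to the first CANreduce study for it. The abstract uses the same unit. Table 4 schedules quantity at baseline (t0), week 6 (t1) and month 3 (t2).

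Consumption Diary explains the unit. Participants enter "how much they actually did use in past days in terms of the number of individually standardized joints". On timing it says "This individual joint is defined at the start of the program". The participant chooses a form (indoor, outdoor or resin), with or without tobacco, and one of "six different amounts of the substance varying from 67 mg to 500 mg". It then states: "Overall, there are 36 different photos made for this selection procedure".

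Measurements describes the menu differently: the choice is "between five different standard joints for each category (1/10 g, 1/6 g, 1/4 g, 1/3 g, and 1/2 g content pictures". It also says that the participant's joint is presented together with "the fraction amount in grams". So the mass of the chosen joint is known, but neither section says that counts are multiplied by it.

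The diary is described as part of the two active arms. Treatment-as-usual (TAU) participants get the program only after 3 months.

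**The concern.** A standardized unit should mean the same thing for everyone who is averaged. Here each participant sets the unit, so ten joints may be 0.67 g for one person and 5 g for another. Data Analyses plans arm comparisons of the secondary continuous outcomes, and the Hypotheses section extends the same expectations to the secondary cannabis outcomes. If quantity is analysed as a raw count, an arm mean mixes unlike amounts, and it is unclear whether a difference between arms is a difference in cannabis consumed.

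The outcome matters because entry requires only weekly use, so daily users are eligible. A participant who still uses every day but uses less shows no change on the 7-day primary outcome. Quantity is where that reduction would appear.

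The TAU arm raises a further question. A joint defined when the program starts has no stated counterpart in an arm that does not start the program during follow-up.

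**Working it through.** **Inputs.** Joint content 67 to 500 mg in six sizes (Consumption Diary); 100 to 500 mg in five sizes (Measurements); 36 photos (Consumption Diary); d = 0.30, two-sided 5%, 80% power, 176 per arm (Sample Size Calculation). The joint counts in step 3 are assumed, because the article gives none.

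**1. The plan's own figures.**
- Photos: 3 forms × 2 (with or without tobacco) × 6 sizes = 36, which matches. Five sizes would give 3 × 2 × 5 = 30. The photo count therefore fits the six-size menu and not the five-size one.
- Sample size: a two-sample t-test with d = 0.30 needs 175.4, rounded up to 176 per arm (power 0.801), and 3 × 176 = 528. This reproduces. It does not depend on the quantity outcome.

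**2. Spread of the unit.**
- Six-size menu: 500 / 67 = 7.46.
- Five-size menu: 500 / 100 = 5.
- Ten joints a week: 10 × 67 = 670 mg against 10 × 500 = 5,000 mg.

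**3. Mean count against mean mass.** Let participant i have joint mass m and change in weekly count Δc. The change in mass is m × Δc, so over a group:

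mean(m·Δc) = mean(m) × mean(Δc) + cov(m, Δc)

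Mean count and mean mass must agree in direction only if the covariance term is small. Take two participants, each keeping a fixed joint. A has the smallest joint and goes from 14 to 7 a week; B has a 500 mg joint and goes from 7 to 9.

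| | Before | After | Change |
|---|---|---|---|
| Mean count | (14 + 7)/2 = 10.5 | (7 + 9)/2 = 8.0 | −24% |
| Mean mg, A at 67 mg | (938 + 3,500)/2 = 2,219 | (469 + 4,500)/2 = 2,484.5 | +12% |
| Mean mg, A at 100 mg | (1,400 + 3,500)/2 = 2,450 | (700 + 4,500)/2 = 2,600 | +6% |

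Check with the formula for the 67 mg case: mean(m) = 283.5, mean(Δc) = −2.5, product −708.75; covariance = 216.5 × 4.5 = 974.25; sum = +265.5 mg, which equals 2,484.5 − 2,219.

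The illustration shows that divergence is possible under either menu, with no change of unit within a person. It does not say how likely divergence is.

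**4. Within one person.** With a fixed reference joint, m is constant, so the percentage change in count equals the percentage change in mass.

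**The case against.** The strongest reply has four parts.

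**The reference joint is a measuring unit, not a tally.** The diary asks for use in terms of a joint fixed at the start and shown with a ruler and its gram content. This stands. A reader might infer that someone who goes from 14 joints of 500 mg to 14 of 250 mg would show no change, or that going from 10 joints of 250 mg to 12 of 100 mg would raise the count by 20% while use falls by 52%. The documents do not support either. Against a 500 mg reference, the first is entered as 14 × 250 / 500 = 7 joints. Against a 250 mg reference, the second is 12 × 100 / 250 = 4.8 joints, a fall of 52%. The first inference needs a respondent who ignores the reference; the second needs that or a re-selection that the article does not describe.

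**Randomisation balances joint size in expectation.** This also stands, so a reader should not infer systematic bias between arms. It does not make counts and grams the same estimand: if the effect on counts differs by joint size, the covariance term differs between arms.

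**A log-link model with a participant-level intercept absorbs a fixed personal multiplier.** This largely stands for ratio-type contrasts. However, Data Analyses makes the linear mixed model the default for continuous outcomes, where the unit is not absorbed in this way. The article gives no variances, so the amount of added noise cannot be computed, and grams could be the more variable scale.

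**The conversion may be given in the cited study or in a fuller plan.** It may be. But the article does more than leave a derivation open: it names joints as the unit, in the abstract and again in Measurements.

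**Conclusion.** The point holds between participants. As written, the quantity outcome is a count in personal units that differ up to 7.5-fold (5-fold with the Measurements menu), with no stated conversion. Arm means of that count need not track the mean amount of cannabis used. No within-person reversal is shown, provided that use is reported against the fixed reference joint. Nor is bias between arms shown: the cost is noise of unknown size and an unclear estimand.

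The reach is one secondary outcome. Days of use in the preceding 7 days and the total of 528 are untouched. The conclusion rests on reading the outcome in the unit that the article names; if a fuller plan already converts to grams, only the wording and the menu mismatch remain. The opposite movements of −24% and +12% come from assumed counts and show possibility, not expected size.

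**What to change.** 1. Reconcile the menus first. Consumption Diary has six sizes from 67 mg and Measurements five from 100 mg; the 36 photos fit six. The conversion depends on which list was in use.
2. Define the outcome as grams of cannabis in the previous week: number of joints times the mass of the participant's selected joint. Keep joint counts as descriptive data.
3. State that the joint is selected at t0 in all three arms, including TAU, which has no diary. Show the same reference joint at t1 and t2. If it is re-selected at a visit, apply the mass recorded at that visit.

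**Cost.** One sentence in the outcome definition and one multiplication by a value that is shown with the joint. Showing the reference joint at follow-up adds at most a screen.

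**Downsides.** Grams equalise mass but not form: indoor, outdoor and resin are still pooled, so form should be described alongside. Grams may also be right-skewed, with zeros from abstinent participants. Data Analyses already allows a suitable distribution for nonnormal continuous outcomes, but since grams are not whole numbers, the choice should be one for continuous data and not a plain count model.

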#### Other Elements

The CANreduce tool further consists of a section with general useful information regarding cannabis, such as physical risks and harm reduction techniques. Furthermore, in some modules, participants are asked to enter their answers to certain exercises (either by clicking on checkboxes or entering text freely). These data are accessible in the section *My Contribution*.

#### Automated Motivational Email Feedback

Each week, participants in intervention arms 1 and 2 will be sent automated motivational email feedback that will contain a reminder to fill out their consumption diary and a direct link to the CANreduce log-in site. If participants do not fill out their diary, they will receive a different reminder email 1 and 3 days later.

Additional emails will be sent out, either automatically or triggered by an administrator or moderator, if certain conditions are met—for example, if an increase in a participant’s cannabis consumption or stalling of consumption reduction is detected—as well as encouraging emails to work with the self-help tool if only a few modules have been completed after 2 and 4 weeks. These feedback emails will also include module suggestions, depending on how subjects have responded in exercises dealing with high-risk situations, cravings, or the pros and cons of their consumption.

In the first CANreduce study [10], participants sometimes discontinued their use of the Web-based self-help tool simply because they had initially aimed for a minimal reduction in consumption and reached this self-set goal within the first few weeks. Therefore, depending on their goals entered into the consumption diary, participants will receive a message encouraging them to reduce their consumption by at least 20 percent over the first week and, if they succeed, to continue that trend in subsequent weeks. Alternatively, participants who do not succeed at reaching their goal will receive the suggestion that they aim for a more modest goal and continue until their final consumption goal is reached.

Another finding from the first version of CANreduce was that some users seek not only to reduce their consumption, but to become completely abstinent. When this goal was achieved early in the program, some felt less inclined to continue with the program. This will be addressed in this study with an automated email, triggered when actual consumption is recorded as zero for several days consecutively in a subject’s consumption diary, encouraging them to nonetheless complete certain modules of importance to their current situation (eg, preventing and dealing with relapses).

One important component of adherence-focused guidance, as defined by Ebert et al [24], is adherence monitoring. Through these mostly automated emails, either encouraging participants to work with the self-help tool or suggesting modules that they have not yet completed, this will be implemented in both active study arms. Another crucial element of adherence-focused guidance is feedback on demand. This too has been implemented in both active study arms by inviting participants at the end of each email to send in any questions that might arise for them during the course of the program. For subjects in the first study arm, this option will also be displayed on the dashboard. Although the content of these nonautomated answers is not specific to either study arm, the format of the emails will differ between study arm 1 and 2, as described next, under *social presence*.

